### Outcomes

The primary outcome is the proportion of participants who receive any dialysis using a home-based therapy (PD or HHD) within 3 months of dialysis initiation. Participants that do not start dialysis or who receive a pre-emptive transplantation at study close will be regarded as non-home-based dialysis outcomes. Participants for which a modality cannot be ascertained will be considered non-home dialysis outcomes. Secondary outcomes include (1) proportion of patients intending to perform a home-based dialysis at 1 year, (2) dialysis knowledge as measured using a locally developed assessment tool (available online as Additional file 1), (3) decision conflict measured using the Decisional Conflict Scale [20], and (4) level of social support measured with the Duke-UNC Functional Social Support Questionnaire [21]. All of the above outcomes will be measured at baseline and 6 and 12 months post intervention.

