### Statistical considerations

In all analyses, participants randomized will be analyzed according to the group to which they were allocated. All ratios and differences will be calculated as the experimental group compared to the control group. These analyses may be modified in the final statistical analysis plan at any time prior to the investigators accessing the study data in an unblinded fashion. The between-group differences in frequencies will be expressed as either absolute risk differences and their associated 95 % confidence intervals and/or by calculating the odds ratio and its associated 95 % confidence interval (exact binomial method). The between-group differences in continuous variables between groups will be assessed using repeated measures analyses. Sensitivity analyses will be performed by assessing the treatment effect after adjusting for baseline risk factors of known or highly suspected association with modality choice. These factors will include age, sex, diabetes mellitus status, socioeconomic strata, availability of a caregiver, presence of cognitive impairment (assessed by the Montreal Cognitive Assessment (MoCA) score [22], frailty [23], health literacy [24], and other comorbidities. To avoid model over-fitting, we will include only an appropriate number of variables (no more than one per 12 home-based dialysis events) and include them in the order in which they are written above. A two-sided *p* value of <0.05 will be regarded as significant without adjustment for multiple comparisons. The baseline probability of selecting home-based dialysis is assumed to be 28 % based on local data. Assuming an alpha value of 0.05, and 80 % power to detect a 22 % absolute difference between the intervention and usual care groups in the proportion of participants starting home-based dialysis, it is estimated that 152 participants would need to initiate dialysis to detect a significant difference between groups. Based on analysis of historical local clinic data on transition rates to ESRD therapies, it is anticipated that 264 participants will need to be recruited and followed for at least 1 year to achieve the required number of events. This recruitment target will be re-evaluated periodically and adjusted as needed based on differences between projected and when actual dialysis starts relative to the total number of recruited participants.

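### Recruitment is steered to 152 dialysis starts, but the primary outcome counts everyone randomised, so reaching 152 does not deliver the stated 80% power, least of all when it is reached by adding recruits

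*Protocol article*

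**What the plan says.** All but one of the relevant statements are in the protocol article under Statistical considerations; the scoring rule is under Outcomes.

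- **Sizing.** The control rate is 28% ("The baseline probability of selecting home-based dialysis is assumed to be 28 % based on local data"). The design aims for "80 % power to detect a 22 % absolute difference between the intervention and usual care groups", and on that basis "it is estimated that 152 participants would need to initiate dialysis to detect a significant difference between groups".
- **Recruitment and follow-up.** From historical clinic data, "264 participants will need to be recruited and followed for at least 1 year to achieve the required number of events".
- **Adaptation.** "This recruitment target will be re-evaluated periodically and adjusted as needed based on differences between projected and when actual dialysis starts". No other response to slow or fast progression is named.
- **Scoring of non-starters.** "Participants that do not start dialysis or who receive a pre-emptive transplantation at study close will be regarded as non-home-based dialysis outcomes".
- **Analysis set.** "In all analyses, participants randomized will be analyzed according to the group to which they were allocated".

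**The concern.** The adaptation rule and the analysis work on different quantities. The rule aims at a number of starters. The analysis compares proportions among all randomised, where each non-starter stays in the denominator as a non-home outcome in either arm. A 22-point difference among starters therefore becomes 22 points multiplied by the fraction who start.

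Two things follow. The trial can meet its target of 152 starts without having the power attached to that target. And the two ways of getting to 152 are not equivalent: recruiting more at a low start fraction leaves the difference diluted, whereas following the same participants for longer raises the start fraction. Only the first is named. At stake is a real effect among people starting dialysis being missed by a trial that believes it is at its planned size.

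**Working it through.** **Inputs from the protocol article:** 28% versus 50% (28 + 22) among starters; two-sided 0.05; 80% power; 152 starts; 264 recruits; non-starters scored non-home; all randomised analysed.

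**Assumptions, not in the document:** 1:1 allocation; the same start fraction f in both arms; slow-start values of f (50%, 40%, 30%), used as a range because no transition rates are given.

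**1. The plan's own figure.** Pooled-variance normal approximation, no continuity correction, mean rate 0.39:

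n per arm = [1.96√(2 × 0.39 × 0.61) + 0.842√(0.28 × 0.72 + 0.50 × 0.50)]² / 0.22² = 75.97, so 76 per arm and 152 in total. This reproduces the plan exactly, as a comparison among starters only.

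**2. The same 152 starts on the stated outcome.** f = 152/264 = 57.6%. The arm rates among all randomised are 0.576 × 28% = 16.1% and 0.576 × 50% = 28.8%, a difference of 12.7 points. With n = 132 per arm and p̄ the mean of the two rates:

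power = Φ{[(p₂ − p₁)√n − 1.96√(2p̄(1 − p̄))] / √(p₁(1 − p₁) + p₂(1 − p₂))} = Φ{(1.455 − 1.157)/0.583} = Φ(0.51) = 69.6%.

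On this outcome, 80% power at f = 57.6% would need about 340 randomised.

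**3. Slow starts: three responses.** The same formula, with arm rates 0.28f and 0.50f. Recruiting to 152 starts means N = 152/f.

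| f | Difference at that f | Stay at 264, no extension | Recruit until 152 starts | Follow the same 264 until 152 start |
|---|---|---|---|---|
| 50% | 11.0 points | 61.7% | N = 304: 67.9% | 69.6% (12.7 points) |
| 40% | 8.8 points | 50.4% | N = 380: 65.8% | 69.6% (12.7 points) |
| 30% | 6.6 points | 38.5% | N = 507: 63.8% | 69.6% (12.7 points) |

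At an equal 152 starts, recruitment recovers less than follow-up by 69.6 − 67.9 = 1.7, 69.6 − 65.8 = 3.8 and 69.6 − 63.8 = 5.8 points. Recruiting to a full 80% would need about 406, 532 or 744 participants at these fractions.

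**4. If later recruits start less often.** Take 264 at 46% plus 150 at 20%. The difference falls from 10.1 to 8.1 points, yet power rises from 57.3% to 64.9%. Power drops below no adjustment only when late recruits almost never start: 200 added at 5% gives 57.2%, and at 0% gives 53.5%, against 57.3%.

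**5. What would restore 80% at 264.** At f = 70% (0.70 × 264, about 185 starts) the difference is 15.4 points and power is 80.5%.

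**6. Exact test.** Fisher's test gives lower power throughout: about 76% for 76 versus 76 starters, 65% at 264 with 57.6% starting, 61% at 380 with 40% starting, and 44% at 264 with 40% starting. The ordering is unchanged.

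**The case against.** A reader might infer that adding recruits itself lowers power. It does not. Compared with staying at 264, it raises power at every start fraction in the table (for example 50.4% to 65.8% at 40%). The difference is small because the start fraction is low. Recruits who start at the same rate as the rest leave it unchanged, and the one-year minimum is not lifted for later entrants.

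A reader might also infer that longer follow-up is ruled out. The text does not say so: one year is a minimum, tied in the same sentence to reaching the required events, and the re-evaluation looks at starts relative to recruits. Extension is permitted, but it is neither named nor triggered.

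The larger loss, from 80% to about 70%, comes from sizing on starters and analysing everyone, and it is present before any slow progression. At equal starts, the choice of lever is worth only about 2 to 6 points, under start fractions the documents do not give. That stands, and it limits how much weight the choice of lever can bear.

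Finally, this is a condensed article, and a detailed closing rule may sit in the full protocol. That excuses missing detail. It does not reconcile the target, the scoring rule and the analysis set, all of which the article states.

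**Conclusion.** The point holds in a limited form. The stated adaptation target of 152 starts does not carry 80% power on the stated primary outcome: it gives about 70% among 264, and about 68%, 66% or 64% if reached by recruiting 304, 380 or 507. These figures rest on the plan's 28% versus 50%, on 1:1 allocation, on equal start fractions in the arms and, for slow starts, on assumed fractions of 50% to 30%. Recruitment is a useful lever, but at equal starts a somewhat weaker one than longer follow-up.

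It would go too far to require the trial to stop at 264 and close at about 185 starts. That needs 70% of participants to start dialysis. Patients intending transplant are eligible and pre-emptive transplants are expected, and nothing in the documents shows that 70% is reachable.

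**What to change.** Amend the sample-size paragraph in Statistical considerations in four respects:

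1. State the power that 152 starts among 264 gives on the all-randomised outcome (about 70% on the plan's own rates), or state the larger number needed for 80%.
2. Base the periodic re-evaluation on the pooled, blinded start fraction and the resulting power on that outcome, instead of on 152 starts alone.
3. Name extension of follow-up beyond the one-year minimum as a lever alongside recruitment.
4. Set study close so that the starters being counted have completed the 3-month window in the primary outcome.

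The roughly 185 starts among 264 can be quoted as a benchmark, but not as a mandatory closing rule. The change is a short amendment using counts the plan already monitors. Its price is a less favourable stated power and possibly a later close.

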## Discussion

Patients with advanced CKD face what can be an overwhelming decision regarding their ultimate choice of dialysis modality. Home-based modalities are less costly and may provide a better quality of life for most patients. However, many Ontario programs are struggling to meet the provincial target of a 40 % home dialysis prevalence rate. Similar struggles have been noted in other jurisdictions. The objective of this intervention is to provide a supportive environment that is meant to encourage and support a decision to choose a home-based modality for patients with advanced CKD using a variety of methods, including informational, decisional, and social support utilizing an IHCA as a framework. This study will also evaluate whether such a tool has an effect on participants’ knowledge, sense of social support, and perceived decisional conflict. The findings from this study will help to inform whether such a tool would be effective in encouraging the use of home-based modalities in this population. The study will have the potential to expand on which, if any, baseline patient factors predict utilization of home-based modalities. From a payer perspective, more than 10,000 patients are on dialysis in Ontario of which the majority is using facility-based HD (>75 %). If this IHCA is an effective educational tool, this would result in improved patient outcomes and substantial healthcare cost-savings. The estimated 10-year provincial cost-savings if the home dialysis proportion increased to 40 % is over US$133 million. The IHCA will be a portable, easy to use, and inexpensive tool making it easily implementable across centers in Ontario and elsewhere.

In end-of-study knowledge translation, we intend to provide information and tools to promote the access and utilization of the website for all CKD programs in Canada. The tool will also be made available through the Kidney Foundation of Canada, the Canadian Society of Nephrology websites, and provincial agencies including the Ontario Renal Network.

## Abbreviations

CKD: chronic kidney disease
eGFR: estimated glomerular filtration rate
HD: hemodialysis
HHD: home hemodialysis
IHCA: interactive health communication application
MoCA: Montreal Cognitive Assessment
PD: peritoneal dialysis
WISHED: web-based IHCA for successful home dialysis
